## Abstract

Waist girth (WG) represents a quick, simple, and inexpensive tool that correlates with excess of fat mass in humans; however, this measurement does not provide information on body composition. The evaluation of body composition is one of the main components in the assessment of nutritional status. Indeed, the use of anthropometry-based equations to estimate body fat and fat-free mass is a frequent strategy. Considering the lack of validation in the Colombian population, the aim of this research study (the F20 Project) is to externally validate WG-based equations (e.g., relative fat mass), and also to develop and validate new models that include WG to estimate body composition in Colombian adults compared to DXA. This cross-sectional study will be carried out following the guidelines for Strengthening the Reporting of Observational Studies in Epidemiology–Nutritional Epidemiology (STROBE–nut). Using stratified probabilistic sampling, the study population will be adults with different levels of physical activity residing in Medellín and its metropolitan area. The results of this study will not only validate the estimation performance of the current WG-based equations, but they will also develop new equations to estimate body composition in the Colombian population. This will improve professional practice in health, exercise, and sports sciences (ClinicalTrials.gov ID #NCT05450588).

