### 1.2. Objectives

The use of equations to estimate body composition is a frequent strategy since it represents a doubly indirect method with a good correlation to the methods mentioned above. However, this leads to the question of whether current WG-based equations are valid for estimating fat mass and fat-free mass in the Colombian population with different levels of physical activity? On the other hand, would it be advantageous to develop new models to obtain a specific equation for the Colombian population? Thus, the aim of this study will be twofold: (i) externally validate the current WG-based equations to estimate fat mass and fat-free mass as compared with DXA, and (ii) develop new models to estimate fat mass and fat-free mass using the WG as a predictive variable, and subsequently validate the new equations in the Colombian population with different levels of physical activity.

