### 2.7. Study Size

According to Knofczynski and Mundfrom [53], to obtain (at least) a coefficient of determination (R^2^) of 0.5 with an excellent level of prediction using 3 independent variables, a total of 130 participants will be needed. Stratified probability sampling techniques will be used. Thus, the total number of participants will be divided into three strata following optimal allocation methods. A fixed cost has been assigned for each stratum (sedentary persons, C1; physically active subjects, C2; and athletes, C3, given that C3 > C2 > C1) to calculate the sample size of each population using Lagrange multipliers, given by the expression:(1)$$nh=n\;\frac{NhSh/\surd Ch}{\sum_{h=1}^{L}NhSh/\surd Ch},\;h=1,\;2,\;\ldots ,\;L$$
where, the values of *n_h_* correspond to the sample units for each stratum, *N_h_* is the maximum number of participants allowed, *C_h_* is the constant cost in all strata, *L* is the number of strata, and *S_h_* is the population quasi-variance of stratum *h*. The values obtained for the sedentary group are *n* = 54; for the physically active population group, *n* = 43; and for the athlete group, *n* = 33. To validate the new equation, the development/validation ratio will be 70/30 over the number of subjects participating in the study.

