### 2.8. Statistical Methods

The descriptive analysis of the anthropometric characteristics of the study population will be reported as means, standard deviations, and 95% confidence intervals. First, the total sample of participants will be used for the external validation of the RFM (to estimate whole-body-fat percentage) [26] and the Takai et al., equation (to estimate fat-free mass) [35]. A correlation analysis will be performed by calculating Pearson’s r, intraclass correlation coefficient (ICC), concordance correlation coefficient (ρ_c_), adjusted coefficient of determination (aR^2^), and root mean squared error (RMSE) as compared to DXA measurements. Smaller values of standard error of the estimate (SEE) and RMSE will indicate that the estimated values are closer to the DXA measurements. Bland–Altman diagrams will be used for the concordance analysis. This is a procedure to determine whether two measurement methods, X and Y, agree sufficiently to be declared interchangeable (D = X − Y). The mean of these differences represents the systematic error (bias), while the variance of these differences (1.96 SD) measures the dispersion of the random error.

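### Agreement is judged on pooled figures whose activity mix (54/43/33) is set by the allocation formula, so they do not by themselves show validity across activity levels; Sections 2.5.3 and 2.8 also conflict on who is pooled

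*Protocol article*

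**What the plan says.** - **Design.** The Abstract states: "Using stratified probabilistic sampling, the study population will be adults with different levels of physical activity residing in Medellín and its metropolitan area".
- **Question.** Section 1.2 asks whether the current equations are "valid for estimating fat mass and fat-free mass in the Colombian population with different levels of physical activity".
- **Allocation.** Section 2.7 says that "a total of 130 participants will be needed" and that "the total number of participants will be divided into three strata following optimal allocation methods". The formula makes n_h proportional to N_h S_h / √C_h. Costs are only ordered ("given that C3 > C2 > C1"). N_h "is the maximum number of participants allowed", and S_h "is the population quasi-variance of stratum" h. No values are given for any of the three. The result is 54 sedentary, 43 active and 33 athletes.
- **External validation.** In Section 2.8 "the total sample of participants will be used for the external validation of the RFM", and the same sentence covers the fat-free-mass equation. Bias is the mean of the differences and spread is 1.96 SD.
- **New equation.** Section 2.8 fits it by ordinary least squares and by Bayesian regression, with at most three predictors. Activity level is one candidate. Performance is then tested in the validation sample, which Section 2.7 sets at 30% of all participants.
- **Section 2.5.3** says something different about the existing equations: RFM for sedentary and active participants, the fat-free-mass equation for athletes.

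**The concern.** The sample shares of the three groups are a product of the design. They are not the shares in any population, and N_h as defined cannot supply those shares. A mean difference, RMSE or pair of limits computed over everyone is an average over that mix. If an equation errs by the same amount at every activity level, the mix does not matter. If it errs differently, the pooled figure would change with a different budget split, and errors of opposite sign partly cancel.

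The study question is about people at different activity levels, and Section 4 names clinical nutrition, sports and public health as the intended uses. A practitioner in any one of these needs the error for that kind of person. The 30% hold-out has, on average, the same mix as the development set, so a pooled check there would not reveal the problem either.

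**Working it through.** **1. The plan's own figures.** 54 + 43 + 33 = 130, which agrees with the stated total. Shares: 54/130 = 41.5%, 43/130 = 33.1%, 33/130 = 25.4%. The allocation itself cannot be recomputed, because N_h, S_h and C_h have no values. It implies only that N_h S_h / √C_h stands in the ratio 54/33 : 43/33 : 1 = 1.64 : 1.30 : 1.

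**2. Who is in each analysis, under each section.**

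| Analysis | If 2.8 governs | If 2.5.3 governs |
|---|---|---|
| RFM | 130, of whom 25.4% athletes | 97 (55.7% sedentary, 44.3% active), no athletes |
| Fat-free-mass equation | 130, of whom 25.4% athletes | 33, all athletes |
| New equation, hold-out | 39, about 10 athletes (0.3 × 33 = 9.9) | the same |

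The two sections cannot both hold for the existing equations. The new equation pools all three strata either way.

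**3. How a pooled figure depends on the mix (illustration).** With stratum share w_h, stratum bias b_h and a common within-stratum SD s of the differences:

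- pooled bias = Σ w_h b_h
- pooled RMSE = √(s² + Σ w_h b_h²)

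Assumptions: s = 3.51 points, borrowed from the RFM RMSE in Section 1.1; the b_h are invented; the comparison mix 60/38/2 is also an assumption.

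*Bias +3 sedentary, +1 active, -1 athletes.*
- Recruited mix: (54×3 + 43×1 - 33×1)/130 = 172/130 = 1.32.
- Mix 60/38/2: 1.80 + 0.38 - 0.02 = 2.16.
- RFM in non-athletes only (2.5.3): (162 + 43)/97 = 2.11.

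The 1.32 describes no stratum and hides a change of sign.

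*Bias 4 in athletes only, with 2.8 governing.*
- Recruited mix: bias 4 × 33/130 = 1.02; RMSE √(12.32 + 0.254×16) = 4.05.
- Mix 60/38/2: bias 0.08; RMSE √(12.32 + 0.02×16) = 3.56.
- The pooled 1.02 also understates the athletes' own error of 4.

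**4. When it matters little.** With an athlete-only bias of 1 point and s = 3.5, pooled RMSE is 3.54 in the recruited mix, against 3.50 to 3.51 with athletes at 1% to 10%.

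**5. Precision of stratum results.** The 95% half-width for a bias is t × s/√n:

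| Group | n | Half-width in units of s | At s = 3.51 points |
|---|---|---|---|
| All | 130 | 0.17 | 0.61 |
| Sedentary | 54 | 0.27 | 0.96 |
| Active | 43 | 0.31 | 1.08 |
| Athletes | 33 | 0.35 | 1.24 |
| Athletes in hold-out | 10 | 0.72 | – |

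The last cell is blank because the new equation predicts fat mass and its s is unknown.

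**The case against.** A reader might infer that every agreement statistic will describe a sample with 25% athletes, and that all of them must therefore be reweighted to population shares. The documents do not support this.

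- **Section 2.5.3 limits its reach.** If that section governs, RFM is tested on no athletes and the fat-free-mass equation on athletes only. The 25% mix then applies to the new equation alone. This stands.
- **Some of it rests on silence.** The total sample, the mean difference and least squares are stated. The absence of weights and of stratum results is only unmentioned, and a full analysis plan may cover it. This stands in part: what the article does state still makes a pooled figure the basis for judging the equations.
- **Activity level is a candidate predictor.** A correctly specified model that contains the stratifying variable does not need weights, so it does not follow that the new equation will be biased. That would require activity to drop out and body fat to differ by activity at equal predictors; the documents establish neither. However, the three-predictor limit means activity may drop out, and hold-out RMSE and limits follow the recruited mix in either case.
- **The target is not declared as a prevalence-weighted average.** Deliberate coverage of three activity levels is a reasonable design for an individual-level equation. This stands.
- **Population weights cannot be built from this design.** No shares are given, and N_h is a cap. Under Section 2.3, adults with high IPAQ activity who are not club athletes belong to no stratum. Recruitment is by open call, through trainers of one gym chain and through club contacts. Weighted figures would look representative without being so. This stands, and it rules out weighting as the main remedy.

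**Conclusion.** The concern holds in a limited form. The strata are sized by allocation and not by population share, and Section 2.8 rests its conclusions on pooled samples. If error differs by activity level, the pooled bias, RMSE and limits reflect the recruited mix and can conceal opposite errors, so they do not alone answer the question in Section 1.2. Sections 2.5.3 and 2.8 contradict each other on the samples for the existing equations, and that must be settled first.

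The size cannot be computed from the documents. In the illustrations, the pooled bias differs from that under the assumed alternative mix by about 0.8 to 0.9 points (1.32 against 2.16; 1.02 against 0.08). For a 1-point difference confined to athletes, RMSE barely moves. All of this depends on assumed stratum biases, assumed shares and a borrowed SD. It is an inexpensive improvement to the analysis and does not invalidate the design.

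**What to change.** 1. Reconcile Sections 2.5.3 and 2.8: state for each existing equation which strata it is applied to.
2. In Section 2.8, report bias, RMSE and limits of agreement with confidence intervals separately for each activity stratum to which an equation is applied, for the existing and the new equations. Base the validity conclusions on these.
3. Label any pooled figure as describing the recruited mix only.
4. If activity level is not in the selected equation, report that equation's bias in each stratum.
5. Optionally, add a share-weighted overall bias and mean squared error as a sensitivity analysis only, with a cited source and a range of shares. Note that weighting does not correct the non-random recruitment in Section 2.3. At the assumed 60/38/2 the interval for the weighted bias would be √(130 × ΣW_h²/n_h) = 1.14 times as wide, with equal within-stratum SDs.

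Cost: wording only, no new data. The stratum intervals are wider: for bias, about twice as wide for 33 athletes as for all 130 (0.35 against 0.17 SD). With about 10 athletes in the hold-out, the new equation's athlete result will be imprecise and should be presented as such.

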## 1. Introduction

The evaluation of body composition is one of the main components in the assessment of nutritional status under the ABCDE model, which considers anthropometric, biochemical, clinical, dietary, and environmental (i.e., socioeconomic status, lifestyle, etc.) aspects as fundamental when analyzing an individual. In fact, considering that the nutritional status of an individual is influenced by endogenous and exogenous factors, the ABCDE model is recommended and valid in both community and clinical nutritional practice [1], as well as at the sports level [2]. Although obesity is currently defined as a “chronic, progressive, relapsing, and treatable multi-factorial, neurobehavioral disease, wherein an increase in body fat promotes adipose tissue dysfunction and abnormal fat mass physical forces, resulting in adverse metabolic, biomechanical, and psychosocial health consequences” [3], the criteria currently used do not allow for the identification of excess adipose tissue. The Body Mass Index (BMI) is one of the most widely used anthropometric indices for predicting nutritional status and the classification of obesity; however, it presents certain errors in its interpretation since it does not differentiate the body composition of a subject, but only relates body mass and stature [4,5]. The ratio of body mass to stature squared has been shown to be useful for large populations; however, adiposity only increases as a function of stature in children, but in adults it is influenced by lean mass. Therefore, it is currently claimed that BMI is not a valid indicator of an individual’s nutritional status [6].

Various assessment methods are used to evaluate body composition, including direct (dissection of cadavers), indirect (magnetic resonance imaging (MRI); computerized axial tomography (CAT); dual-energy X-ray absorptiometry (DXA)) and doubly indirect methods (anthropometry and bioelectrical impedance analysis (BIA)) [7]. Currently, the four-component model (4C Model) involves an independent assessment of body density, total body water, and bone-mineral content, and is therefore commonly described as the most accurate measure because it combines the advantages of different methods [8]. Although there are several indirect methods that allow a more accurate evaluation of body composition and density, in practice there are certain limitations related to the high cost of the equipment, the control of radiation exposure, and the technical maintenance/specialization required for its use [9]. In this regard, anthropometric measurements (skinfolds, girths, lengths, and diameters) have been used to evaluate morphology, body composition, and maturation status, among other aspects. Therefore, anthropometry provides practitioners with a tool that serves to monitor physical performance or health-related outcomes, while taking into account the particular characteristics of the individuals.

### 1.1. Background Rationale

Kinanthropometry is a discipline that analyzes the use of body measurements and their relationships with other parameters of health or human movement. It is considered to be a simple technique that also helps to estimate body composition (e.g., body fat percentage) from regression equations [10]. Among the anthropometric variables that have been used for the development of the most common equations in current daily practice (i.e., body mass, stature, age, sex, and skinfolds), it should be noted that waist girth (WG) has been used to a lesser extent, even though it represents a quick, simple, and inexpensive tool for predicting excess fat mass in humans [11]. The WG is the girth at the narrowest position in the abdominal area between the tenth rib and the iliac crest, as described in the International Standards for Anthropometric Assessment established by the International Society for the Advancement of Kinanthropometry (ISAK) [12]. WG is considered a determining variable in the diagnosis of metabolic syndrome as it is directly related to visceral fat [13] and has stronger associations with health-risk indicators [14]. WG has been used to diagnose abdominal obesity and as an indicator of cardiovascular risk [15,16,17]. Although this measurement cannot provide information on body composition, absolute values of this girth have shown a high correlation with the percentage of body fat obtained by DXA, which has positioned WG as an optimal indicator for the evaluation of body fat in different populations [18,19,20,21]. The presence of central obesity is defined based on the proposed cutoff for Latin-American adults (WG ≥ 90 cm in women and WG ≥ 94 cm in men) [22].

Several authors have concluded that regression equations that use WG as a predictive variable appear to estimate body fat percentage more accurately [23,24,25]. In this sense, the relatively recent efforts of some research groups have developed equations that include WG as an independent variable to estimate fat mass and fat-free mass. On the one hand, Woolcott and Bergman [26] developed and validated a simple equation, named relative fat mass (RFM), to estimate the percentage of total body fat using the WG, stature, and sex of the American adult population (64 − (20 × (stature [m]/WG [m])) +  (12 × sex [0 for male and 1 for female])). The population data were extracted from the National Health and Nutrition Examination Survey (NHANES) between 1999 and 2006. The performance of RFM as an easy and useful tool in clinical practice, with a better correlation to DXA than BMI (RFM: R^2^ = 0.84; RMSE = 3.51% vs. BMI: R^2^ = 0.36; RMSE = 7.04%) has been validated in adults [27], children between 8 and 14 years old, and adolescents between 15 and 19 years old [28], obese subjects [29,30], and individuals with Down syndrome [31], among other populations at cardiovascular risk [32,33]. It is worth noting that the RFM defines obesity according to the cutoff points of the DXA measurements, to the point that following the rounded thresholds of the RFM baseline, the current recommendation for diagnosing obesity and predicting the risk of death with this parameter is 40% for women and 30% for men [34]. On the other hand, Takai et al. [35] developed an equation to estimate fat-free mass in male athletes using some indices as independent variables, including WG/body mass and stature/WG. The equation developed by these authors was validated with a sample of 48 athletes from different disciplines and showed a high correlation (R^2^ = 0.900, SEE = 2.3 kg [3.8%]) with the fat-free-mass data obtained by DXA (FFM (kg) = 0.883 × Body mass/WG [kg/m] + 43.674 × WG/Stature [cm/cm] − 41.480). The results of this study demonstrated that an equation using body mass and stature ratios with WG as independent variables is applicable and useful for predicting fat-free mass in male athletes.

In Colombia, there are no studies that have validated these WG-based equations for estimating body composition. A recent study performed the concurrent validation of 5 equations frequently used to estimate the percentage of body fat in young Colombian athletes of both sexes (Slaughter, Durnin–Rahaman, Lohman, Johnston, and the 5C Model by Kerr) when comparing the results against DXA measurement [36]. Interestingly, the Durnin–Rahaman and Johnston equations showed good-to-excellent validity with low bias in the population analyzed, but none of these equations used WG as a predictor variable. Only one study in Colombian adult women utilized anthropometric data (body mass, stature, skinfolds, and girths (including WG)) and hydrodensitometry evaluation to subsequently develop different linear regression models to estimate the percentage of body fat [37]. Cross-validation of the developed models showed that both Equation (1) (SEE = 2.84%; R^2^ = 0.71) and Equation (2) (SEE = 3.06%; R^2^ = 0.67) had a low standard of error in the estimation of the percentage of body fat and moderate–high values in the coefficient of determination. However, this research has two important limitations that are worth mentioning in regard to generalizability and interpretation. First, the research used Lohman’s anthropometric protocol—instead of the current ISAK recommendations that are promoted by international entities, such as the World Health Organization [38] and the International Olympic Committee [39]; in fact, this protocol is less reproducible/standardized and less recommended, and it is increasingly falling out of use because it includes invasive measurements, such as the midaxillary skinfold—which was a variable in one of the generated models. Second, hydrodensitometry as a reference methodology has some disadvantages, including the exclusion of participants who do not complete the underwater weighing test, as well as the fact that it is a methodology for estimating body density but not for estimating fat percentage. Importantly, the use of the Siri equation to estimate body-fat percentage implicates an additional estimation, so the values reported may not be accurate [40].

### 1.2. Objectives

The use of equations to estimate body composition is a frequent strategy since it represents a doubly indirect method with a good correlation to the methods mentioned above. However, this leads to the question of whether current WG-based equations are valid for estimating fat mass and fat-free mass in the Colombian population with different levels of physical activity? On the other hand, would it be advantageous to develop new models to obtain a specific equation for the Colombian population? Thus, the aim of this study will be twofold: (i) externally validate the current WG-based equations to estimate fat mass and fat-free mass as compared with DXA, and (ii) develop new models to estimate fat mass and fat-free mass using the WG as a predictive variable, and subsequently validate the new equations in the Colombian population with different levels of physical activity.

## 2. Methods

### 2.1. Study Design

This will be a cross-sectional study based on the Strengthening the Reporting of Observational Studies in Epidemiology–Nutritional Epidemiology (STROBE–nut) guidelines, an Extension of the STROBE Statement [41]. This study (the F20 Project) will test the validity of current WG-based equations and will develop new models to estimate fat mass and fat-free mass as compared with DXA as a reference criterion.

